## **9. STAFF TRAINING**

All study staff will be trained on the study protocol, including administration of study medication, symptom monitoring, and participant assessment prior to initiation of recruitment and enrollment. Training took place in-person in St. Petersburg and via webinars.

**Health**

**NIAAA Award Number: U01AA021989**

**Clinicaltrials.gov Registration: NCT01934803**

**Boston University Medical Campus IRB Protocol Number: H-31901**

**Enrollment Dates: October 2013 – June 2015**

**Statistical Analysis Plan (SAP) Version Date: 10/26/2018**

## **SAP Revision History**

| Date of revision | Section number changed | Description and reason for change                                                                         |
|-------------------------|-------------------------------|------------------------------------------------------------------------------------------------------------------|
| 6/8/2017                | 5.3 Missing Data              | Updating multiple imputation plan to clarify details on specific variables will be included in imputation model. |

|            |                         |                                                                                                                           |
|------------|-------------------------|---------------------------------------------------------------------------------------------------------------------------|
| 8/15/2017  | 5.3 Missing Data        | Adding predictors for missing outcome data.                                                                               |
| 1/26/2018  | 5.1 Outcome Definitions | Posthoc replacement of LPS with IFABP another marker of microbial translocation, due to inability to conduct LPS testing. |
| 2/28/2018  | 5.5 Harms               | Adding posthoc plans for mortality analyses using actual mortality events.                                                |
| 4/13/2018  | 5.4 Additional Analyses | Adding posthoc plans for analyzing individual VACS components.                                                            |
| 10/26/2018 | 5.1 Outcome Definitions | Replacing 16srDNA with LBP, due to the lab having trouble extracting rDNA from study samples.                             |

## SECTION 1: INTRODUCTION

### 1.1 STUDY HYPOTHESES

We hypothesize that as compared with placebo, participants receiving zinc supplementation will have significantly:

Hypothesis 1- Smaller change in VACS (Primary);

Hypothesis 2- Greater change in CD4 cell counts (Secondary);

Hypothesis 3- Lower Reynolds risk score (Secondary);

Hypothesis 4- Lower biomarker levels of microbial translocation and inflammation (Secondary).

## SECTION 2: STUDY METHODS

### 2.1 STUDY DESIGN

ZINC is a double-blinded randomized placebo-controlled trial of zinc supplementation (Zinc for INflammation and Chronic disease in HIV [ZINC]) among HIV-positive heavy drinkers in Russia to evaluate the efficacy of zinc to 1) improve markers of mortality, as measured by the VACS index; 2) slow HIV disease progression, as measured by CD4 cell count; 3) improve markers of coronary heart disease (CHD) risk, as measured by the Reynolds risk score and; 4) decrease microbial translocation and inflammation, as measured by serum biomarkers. Participants will receive study medication over 18 months, with study visits occurring at 6, 12, and 18 months post enrollment, and shorter medication adherence visits at 6 weeks, 12 weeks, 9 months, and 15 months. ZINC RCT is nested within the Russia ARCH cohort of the Uganda, Russia, Boston Alcohol Network for Alcohol Research Collaboration on HIV/AIDS (URBAN ARCH) Consortium, which aims to understand how alcohol use impacts people affected by HIV and develop interventions to reduce alcohol use and alcohol and HIV-related consequences in this population.

### 2.2 RANDOMIZATION

See section 3.2 of Study Protocol

### 2.3 SAMPLE SIZE

See section 2.7.A. of Study Protocol

### 2.4 FRAMEWORK

This study will use a superiority hypothesis testing framework. We will test whether zinc: 1) improves markers of mortality, as measured by the VACS index; 2) slows HIV disease progression, as measured by CD4 cell count; 3) improves markers of coronary heart disease (CHD) risk, as measured by the Reynolds risk score and; 4) decreases microbial translocation and inflammation, as measured by serum biomarkers, compared to placebo.

## **2.5 STATISTICAL INTERIM ANALYSES AND STOPPING GUIDANCE**

None

## **2.6 TIMING OF FINAL ANALYSES**

All outcomes analyzed collectively once all 18-month outcome data have been collected and cleaned.

## **2.7 TIMING OF OUTCOME ASSESSMENTS**

See section 3.5A of Study Protocol

# **SECTION 3: STATISTICAL PRINCIPLES**

## **3.1 Confidence intervals and P values**

Statistical tests will be 2-sided and will be performed using a 5% significance test. Confidence intervals will be reported for measures of effect.

## **3.2 Adherence and protocol deviations**

Participants will be considered adherent to study intervention if they self-report  $\geq 80\%$  adherence on the visual analog scale (VAS) for  $\geq$  three study visits. Descriptive statistics on the percent of participants adherent will be summarized by randomized group.

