#### 3.4.B. ADHERENCE

Medication adherence will be assessed at each study visit using direct (Riboflavin) and indirect (pill counts and self-report) measures.

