###### *Self-Report*

Medication adherence will also be measured through self-report using the modified Adult AIDS Clinical Trial Group (AACTG) ART adherence questions. At each post-baseline study visit participants will be

asked to draw a line on a paper ruler, numbered from 0-100, to indicate the number best representative of how much of the study medication they have taken in the past 6 weeks. Participants will also be asked questions about the longest period of time in which they consistently took the study medication, if they stopped taking the medication, and if they took more than one pill of study medication on any day in the past 6 weeks.

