The main analysis evaluating the impact of zinc on the primary study outcome (i.e., change in VACS index) will use multiple regression models that include randomization group (i.e., zinc vs. placebo) as the main independent variable. The regression analyses will control for the two block randomization stratification factors: heavy alcohol consumption during the past week and gender. In addition, the models will control for baseline characteristics that differ between groups in order to avoid confounding. Potential confounders of interest, measured at baseline, include demographics, past month alcohol use, age, gender, anti-inflammatory medication use, cardiovascular disease risk factors, HCV status, substance use (e.g., alcohol, smoking, cocaine), CD4 cell count, HIV-1 RNA, duration of awareness of HIV infection, and socioeconomic status. If the data are normally distributed, multiple linear regression models will be used. However, if the distribution is skewed, transformations of the data will be performed (e.g., log transformation). If an appropriate transformation is not identified, a median regression model will be used. The secondary outcomes, including HIV disease progression, as measured by change in CD4 cell count (Aim 2); the Reynolds risk score (Aim 3); and biomarkers of microbial translocation and inflammation (Aim 4) will be analyzed using the same approach described above. A secondary analysis will be conducted using a per protocol approach that includes only those participants who were adherent with their assigned intervention (i.e., taking zinc or placebo 80% of the time).

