## **3.3 Analysis Populations**

The intention-to-treat (ITT) population will include all randomized participants according to the study group assigned.

The per-protocol population will include all participants meeting the definition of adherence noted in section 3.2 above.

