The main analysis evaluating the impact of zinc on the primary study outcome (i.e., change in VACS index) will use multiple regression models that include randomization group (i.e., zinc vs. placebo) as the main independent variable. The regression analyses will control for the two block randomization stratification factors: heavy alcohol consumption during the past week and gender. In addition, the models will control for baseline characteristics that differ between groups in order to avoid confounding. Potential confounders of interest, measured at baseline, include demographics, past month alcohol use, age, gender, anti-inflammatory medication use, cardiovascular disease risk factors, HCV status, substance use (e.g., alcohol, smoking, cocaine), CD4 cell count, HIV-1 RNA, duration of awareness of HIV infection, and socioeconomic status. If the data are normally distributed, multiple linear regression models will be used. However, if the distribution is skewed, transformations of the data will be performed (e.g., log transformation). If an appropriate transformation is not identified, a median regression model will be used. The secondary outcomes, including HIV disease progression, as measured by change in CD4 cell count (Aim 2); the Reynolds risk score (Aim 3); and biomarkers of microbial translocation and inflammation (Aim 4) will be analyzed using the same approach described above. A secondary analysis will be conducted using a per protocol approach that includes only those participants who were adherent with their assigned intervention (i.e., taking zinc or placebo 80% of the time).

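### The SAP's per-protocol rule (self-reported VAS of at least 80% at three or more visits) does not match the 80%-of-the-time criterion given for the same analysis, and it can admit people off capsules for the final year

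*Supplement*

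**What the plan says.** SAP 3.2 states the rule: "Participants will be considered adherent to study intervention if they self-report" at least 80% "adherence on the visual analog scale (VAS) for" three or more study visits. It gives no denominator and does not say which visits count. SAP 3.3 adds no further condition: "The per-protocol population will include all participants meeting the definition of adherence noted in section 3.2 above".

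SAP 5.2 describes the per-protocol analysis differently, as one that "includes only those participants who were adherent with their assigned intervention (i.e., taking zinc or placebo 80% of the time". Protocol 8.1 has the same parenthesis: "i.e., taking zinc or placebo 80% of the time".

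Protocol 3.4.B (Self-Report) has participants mark a 0-100 ruler at each post-baseline visit to show "how much of the study medication they have taken in the past 6 weeks". The same section says adherence is assessed at each visit by "direct (Riboflavin) and indirect (pill counts and self-report) measures". Only the self-report enters the SAP 3.2 rule.

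**The concern.** A count of three visits with no denominator is not the same criterion as 80% of the time, and the two select different people. The SAP 3.2 rule can be met entirely in the first six months, because no late visit is required. Protocol 3.4.E keeps people who discontinue in follow-up, so someone who stopped early can still contribute an 18-month outcome.

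The per-protocol analysis is there to show what zinc does when it is taken, and SAP 5.4 puts the main interest in the long-term effect at 18 months. If zinc works only while it is taken, each long-stopped participant in the per-protocol set pulls its estimate toward the ITT estimate. A null per-protocol result could then be read as no effect even when taken, which the population as defined could not support.

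**Working it through.** **Inputs**
- Visits: eight including baseline (protocol 3.3), so seven after baseline: weeks 6 and 12, and months 6, 9, 12, 15 and 18 (protocol 2.3, SAP 2.1).
- VAS: asked at each post-baseline visit with a 6-week recall (protocol 3.4.B). Adherence questions are also asked at the short medication visits (protocol 5.2.A).
- Treatment period: 18 months = 18 × 365.25 / 12 / 7 = 78.3 weeks.
- Visit windows (protocol 3.5.A): month-6 visit from 4 to 8 months, month-18 visit from 17 to 21 months.

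**Step 1. Does the SAP 3.2 rule reproduce the stated 80%?** It does not.
- Share of reports needed: 3 / 7 = 42.9%.
- Lowest qualifying mean VAS, with three reports of 80 and four of 0: 3 × 80 / 7 = 34.3. With three reports of 100 and four of 0: 300 / 7 = 42.9.
- Time covered by three recalls: 3 × 6 = 18 weeks; 18 / 78.3 = 23%.
- Visits needed for an 80% rule: 0.80 × 7 = 5.6, so six of seven. Five of seven is 71%.

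**Step 2. A participant who stops at month 6.** Take good reports at week 6, week 12 and month 6, assume steady intake up to month 6 and none after.
- Doses taken at 80% adherence: 0.80 × 6 / 18 = 26.7%. At 100%: 6 / 18 = 33.3%.
- Time off capsules at the endpoint: 18 − 6 = 12 months nominally. By the windows it runs from 17 − 8 = 9 to 21 − 4 = 17 months.
- If the month-6 visit falls at month 4, the doses taken are 17.8% to 22.2%. If it falls at month 8, they are 35.6% to 44.4%.

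This participant is in the per-protocol population under SAP 3.2 and 3.3 and outside it under SAP 5.2.

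**Step 3. How far could the two kinds of rule differ?** The documents give no adherence distribution. As an illustration only, assume independent visits with probability p of a report of at least 80%. The binomial tail for seven visits gives:

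| p (assumed) | at least 3 of 7 | at least 6 of 7 |
|---|---|---|
| 0.5 | 77% | 6% |
| 0.6 | 90% | 16% |
| 0.7 | 97% | 33% |
| 0.8 | 99.5% | 58% |

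Real reports would be correlated within a person, so these figures show only that the choice of count is not a detail.

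**The case against.** **The analysis is secondary and the operative rule is clear.** SAP 3.3 points to SAP 3.2, so a programmer would apply the three-visit rule, and the phrase in SAP 5.2 is carried over from the protocol. This stands as far as it goes: the primary analysis is ITT with multiple imputation and is untouched. But applying the operative rule gives a population that is not the one SAP 5.2 says is analysed, and nothing reconciles them.

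**A narrower reading of study visits.** SAP 2.1 uses that term for months 6, 12 and 18 and calls the others medication adherence visits. On that reading all three long visits would be needed and the month-6 stopper would fail. It is the weaker reading. Protocol 3.3 counts the short checks among the eight study visits, protocol 3.4.B asks the VAS at every post-baseline visit, and a minimum of three is odd if three is also the maximum. Even then the recalls would cover 23% of treatment.

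**Three stronger readings are not supported.**
- A reader might infer that the per-protocol population would consist largely of untreated people. The documents show only that the rule permits such people, not that they are many.
- A reader might take 0.80 × 23% = 18% of doses as the size of the problem. That assumes no capsule outside three recall periods. It is a theoretical extreme, and not an exact floor, because the visit windows allow recall periods to overlap.
- A reader might conclude that pill counts should simply replace the VAS. Leftover pills are handed back, an extra six-week supply is issued, lost pills are replaced (protocol 3.4.C, 3.4.D), and protocol 3.4.A foresees counts above 100%. Riboflavin is expected to be detectable for up to 24 hours. Some assessments may be by telephone (protocol 3.6.A). Scoring every unvisited interval as not taken would also select on retention and would ignore interruptions that the protocol itself directs.

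**Conclusion.** The inconsistency is real and should be fixed. SAP 3.2 and 3.3 accept 43% of the possible reports, covering 23% of the treatment period, where SAP 5.2 and protocol 8.1 require 80% of the time. A participant who took roughly 27% to 33% of the doses and stopped a year before the endpoint meets the rule.

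These figures rest on seven VAS reports, nominal visit times, and steady intake to month 6 followed by none. Dilution toward ITT further assumes that any benefit depends on continued intake. It is a possible consequence whose size the documents do not allow one to state. This is a should-fix point in a secondary analysis.

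**What to change.** Write one definition in SAP 3.2, covering baseline to 18 months with an explicit denominator, and have SAP 5.2 refer to it. Two workable forms use the VAS already collected:
- mean VAS of at least 80 over the seven post-baseline visits; or
- VAS of at least 80% at six or more of the seven.

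They are not equivalent: six reports of 80 and one of 0 give a mean of 480 / 7 = 68.6. One must be chosen. Neither proves intake over the whole period, since seven recalls cover 42 of 78.3 weeks (54%), and the SAP should say so.

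The definition should also state how missed visits are scored, how protocol-directed interruptions (antibiotic courses and pregnancy, protocol 3.3 and 3.4.E) are treated, and whether an observed 18-month outcome is required. Pill-count and riboflavin definitions should be reported as sensitivity analyses, with their limits noted.

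The cost is SAP wording and a derived variable from data already collected, plus a smaller per-protocol population. Enrollment ended in June 2015, so the last 21-month window closed about March 2017, before the SAP date of October 2018. A change made after data collection should be labelled post hoc, with the three-visit rule reported alongside.

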## **3.3 Analysis Populations**

The intention-to-treat (ITT) population will include all randomized participants according to the study group assigned.

The per-protocol population will include all participants meeting the definition of adherence noted in section 3.2 above.

# **SECTION 4: TRIAL POPULATION**

## **4.1 Screening Data**

The following data will be provided for all screened participants: number of patients assessed for eligibility, number of participants enrolled, reasons for ineligibility and non-enrollment.

## **4.2 Eligibility**

See section 2.5 of Study Protocol.

## **4.3 Recruitment**

The CONSORT diagram will present data on number of participants screened, eligible, enrolled, randomized, assigned to each study arm, and completing follow up.

#### 4.4 Withdrawal/follow up

Reasons for discontinued treatment will be presented in the CONSORT diagram/trial profile.

#### 4.5 Baseline Participant Characteristics

Descriptive statistics will be calculated for the following variables at baseline overall and stratified by randomized group: age, sex, heavy alcohol (past week), education, marital status, employment, VACS Index, CD4, Reynolds risk score, IL-6, D-dimer, sCD14, 16sRDNA , smoking status (current, ever, never), BMI, CVD, AST/ALT, FIB4, HCV (test), HVL, hemoglobin, platelets, eGFR, Blood pressure, Total cholesterol, HDL cholesterol, CRP, mother/father MI. For continuous variables, the following will be provided: median, mean, standard deviation, 0th, 25th, 50th, 75th, and 100th percentiles. For categorical variables, frequencies and proportions will be provided. For each primary and secondary outcome, descriptives will also be reported stratified by arm and follow-up time, (note, no testing will be done for any of the above).

### SECTION 5: ANALYSIS

#### 5.1 Outcome Definitions

|                                                                                      |                                                |                     |                   |                   |                 |
|--------------------------------------------------------------------------------------|------------------------------------------------|---------------------|-------------------|-------------------|-----------------|
| Primary (Aim 1)                                                               | VACS Index (change from baseline to 18 months) |                     |                   |                   |                 |
| Secondary (Aim 2)                                                             | CD4 (change from baseline to 18 months)        |                     |                   |                   |                 |
| Secondary (Aim 3)                                                             | Reynolds Risk Score 18 months)                 |                     |                   |                   |                 |
| Secondary (Aim 4)                                                             | IL-6 (18 months)                               | D-dimer (18 months) | sCD14 (18 months) | IFABP (18 months) | LBP (18 months) |
| Secondary: repeated measures of all available follow-up data for each outcome |                                                |                     |                   |                   |                 |
| Secondary: change from baseline to 18 months                                  |                                                |                     |                   |                   |                 |

See section 2.1 of Study Protocol.

#### 5.2 Analysis Methods

The study aims to test the hypothesis that compared with placebo, participants receiving zinc supplementation will have significantly 1) lower VACS index scores; 2) higher CD4 cell counts; 3) lower Reynolds risk score and; 4) lower biomarker levels of microbial translocation and inflammation. The primary outcome is improved markers of mortality, as measured by change in VACS index score between baseline and 18 months. The secondary outcomes are slower HIV

disease progression, as measured by change in CD4 cell count; improved markers of AMI risk, as measured by the Reynolds Risk Score; and lower biomarker levels of microbial translocation and inflammation.

This study will be conducted under the intention-to-treat principle and thus main analyses will include all participants according to their randomized assignment. Descriptive statistics will be calculated for variables at baseline and each follow-up time point. At baseline, participant characteristics will be presented by randomized arm to assess whether there are any differences between groups. Spearman correlation coefficients will be obtained to identify pairs of variables that may be collinear ( $r > 0.4$ ) and would therefore not be included together in regression analyses.

The main analysis evaluating the impact of zinc on the primary study outcome (i.e., change in VACS index) will use multiple regression models that include randomization group (i.e., zinc vs. placebo) as the main independent variable. The regression analyses will control for the two block randomization stratification factors: heavy alcohol consumption during the past week and gender. In addition, the models will control for baseline characteristics that differ between groups in order to avoid confounding. Potential confounders of interest, measured at baseline, include demographics, past month alcohol use, age, gender, anti-inflammatory medication use, cardiovascular disease risk factors, HCV status, substance use (e.g., alcohol, smoking, cocaine), CD4 cell count, HIV-1 RNA, duration of awareness of HIV infection, and socioeconomic status. If the data are normally distributed, multiple linear regression models will be used. However, if the distribution is skewed, transformations of the data will be performed (e.g., log transformation). If an appropriate transformation is not identified, a median regression model will be used. The secondary outcomes, including HIV disease progression, as measured by change in CD4 cell count (Aim 2); the Reynolds risk score (Aim 3); and biomarkers of microbial translocation and inflammation (Aim 4) will be analyzed using the same approach described above. A secondary analysis will be conducted using a per protocol approach that includes only those participants who were adherent with their assigned intervention (i.e., taking zinc or placebo 80% of the time).

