### 2.7.A. SAMPLE SIZE CALCULATION AND POWER

Power was calculated for the overall primary study endpoint (change in VACS index score). Power calculations assumed a two-sided hypothesis test, with a significance level of 0.05. It was expected that 250 participants would be enrolled into the study. We anticipated 20% loss to follow-up due to death and participant withdrawal. Based on the VACS study, the standard deviation of the change in VACS index score from initiation of ART to after one year was 25. We expect the standard deviation will be similar in this study. Given these assumptions and with 200 evaluable participants (assuming 20% loss to follow-up, and 100 participants in each arm), the study is anticipated to have 80% power to detect a difference between the placebo and zinc groups in their mean changes in VACS index score over the 18-month period as small as 10 (e.g. 20 vs. 10 for the placebo and zinc groups, respectively) using a two-sided t-test.

Aim 2: To test the efficacy of zinc supplementation compared to placebo to slow HIV disease progression as measured by CD4 cell count. We anticipate analyzing log transformed values of change in CD4 cell count due to possible skewness in the data. Group differences will be back transformed from the natural log scale and therefore the parameter of interest is the ratio of the mean changes in CD4 cell count from baseline to 18 months for the zinc group relative to the placebo group, where change is defined as CD4 count at baseline - CD4 count at 18 months. The estimated coefficient of variation for the change in CD4 cell count from baseline to 18 months (baseline - 18 months) is 0.20 cells/ $\mu$ L. Given these assumptions, with 200 evaluable participants (100 in the zinc and placebo arms), the study will have 96.3% power to detect a ratio of 0.90 (zinc:placebo) between the mean changes of CD4 counts for the zinc and placebo groups using a two-sided t-test.

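### The outcome's own baseline value is not a prespecified covariate in the primary or secondary models, so precision is given up and its entry is left to an undefined imbalance rule

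*Supplement*

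**What the plan says.** SAP 5.2, with the same text in protocol 8.1, regresses "change in VACS index) will use multiple regression models that include randomization group (i.e., zinc vs. placebo) as the main independent variable". The fixed adjustment is this: "The regression analyses will control for the two block randomization stratification factors: heavy alcohol consumption during the past week and gender". Other baseline characteristics are added when the arms differ on them. The candidates named there include CD4 count and HIV-1 RNA, but not VACS, the Reynolds score or any biomarker. The secondary outcomes follow the same approach. SAP 5.2 also bars pairs of variables with a Spearman correlation above 0.4 from entering a model together.

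SAP 5.1 defines VACS and CD4 as change over 18 months. It defines the Reynolds score, IL-6, D-dimer, sCD14, IFABP and LBP as 18-month values. A separate secondary row lists change from baseline without saying which outcomes it covers.

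SAP 4.5 tabulates baseline characteristics by arm, among them "VACS Index, CD4, Reynolds risk score, IL-6, D-dimer, sCD14", and rules out testing them. IFABP and LBP are not in that list.

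The sample-size section (protocol 2.7.A) rests on an unadjusted comparison of mean changes by t-test.

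**The concern.** A baseline measurement of the outcome is usually its strongest single predictor. A change score subtracts the whole baseline value when, with equal variances, only the fraction rho of it carries over to follow-up. An 18-month level ignores baseline altogether. Either choice leaves variance in the comparison that a baseline covariate would remove.

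The rule for adding unbalanced covariates does not close the gap. The precision gain comes from the correlation between baseline and outcome, not from imbalance, so it is lost whenever the arms happen to be balanced. The rule also has no threshold, so whether baseline VACS enters the primary model would be settled after the data are seen.

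At stake are power for the primary comparison, the width of the intervals for the secondary outcomes, and a primary covariate set that is not fully fixed in advance.

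**Working it through.** **Inputs from protocol 2.7.A**
- Test: "calculations assumed a two-sided hypothesis test, with a significance level of 0.05".
- SD of change: "the standard deviation of the change in VACS index score from initiation of ART to after one year was 25".
- Size: "with 200 evaluable participants (assuming 20% loss to follow-up, and 100 participants in each arm".
- Effect: a mean difference "as small as 10 (e.g. 20 vs. 10 for the placebo and zinc groups, respectively) using a two-sided t-test".
- Claim: "the study is anticipated to have 80% power to detect a difference between the placebo and zinc groups in their mean changes".

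**Assumed, because the documents do not give it:** the correlation rho between baseline and 18-month values, shown from 0.3 to 0.9. Variances are first taken as equal at the two times.

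**Step 1. The plan's own figure.** The standard error is 25 × √(2/100) = 3.54, and 10/3.54 = 2.83. Power is 80.7% by the normal approximation and 80.4% by the noncentral t. The required size is 99 per arm, and 200/0.80 = 250 enrolled. The stated 80% reproduces.

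**Step 2. VACS with baseline added.** Let s be the common SD at each time.
- Variance of change: 2s²(1 − rho).
- Residual variance after adjusting for baseline: s²(1 − rho²).
- Ratio of the second to the first: (1 + rho)/2.

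Holding the SD of change at 25, the adjusted SD is 25 × √((1 + rho)/2).

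| rho | Variance ratio | Adjusted SD | Power, 100 per arm | Detectable difference at 80% power | n per arm for 80% power |
|---|---|---|---|---|---|
| none (as planned) | 1 | 25 | 80.4% | 9.95 | 99 |
| 0.3 | 0.65 | 20.16 | 93.7% | 8.0 | 64 |
| 0.5 | 0.75 | 21.65 | 90.1% | 8.6 | 74 |
| 0.7 | 0.85 | 23.05 | 86.3% | 9.2 | 84 |
| 0.9 | 0.95 | 24.37 | 82.3% | 9.7 | 94 |

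A simulation (4,000 runs per value) gave 81.4% against 93.7% at rho 0.3, 79.9% against 90.0% at 0.5, and 80.1% against 86.2% at 0.7, for change score against baseline-adjusted analysis.

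**Step 3. Unequal variances.** Let k be the baseline SD divided by the 18-month SD. In units of the 18-month variance, the change score has variance 1 + k² − 2·rho·k and the adjusted residual has 1 − rho². The difference is (k − rho)², which is never negative but is zero when k = rho. Example with k = rho = 0.7: 1 + 0.49 − 0.98 = 0.51, and 1 − 0.49 = 0.51, so there is no gain.

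**Step 4. Outcomes analysed as 18-month levels.** The ratio of adjusted to unadjusted variance is 1 − rho²: 0.91 at rho 0.3, 0.75 at 0.5, 0.51 at 0.7 and 0.19 at 0.9. This step does not need equal variances.

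**Step 5. Chance imbalance in baseline VACS if it is left out.** With equal variances, s = 25/√(2(1 − rho)), the standard error of the baseline difference is s × √(2/100), and the change-score estimate shifts by (1 − rho) times the imbalance.
- rho 0.5: s = 25 and the standard error is 3.54. A one-standard-error imbalance shifts the estimate by 1.8 points, and two standard errors by 3.5.
- rho 0.7: s = 32.3 and the standard error is 4.56. The shifts are 1.4 and 2.7 points.

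These compare with a 10-point target. They average to zero over randomisations.

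**The case against.** The plan does provide for imbalance. It will control for baseline characteristics on which the arms differ, names baseline CD4 as a candidate, and gives its candidate list as examples rather than a closed set. Baseline VACS, Reynolds score, IL-6, D-dimer and sCD14 are all tabulated by arm, so any of them could enter. A reader might infer that the models exclude baseline values outright, or that chance imbalance must stay in the estimate. The documents do not support either reading. What remains is that entry is conditional, has no criterion, and could be blocked by the r > 0.4 rule, for example if baseline VACS correlates with baseline CD4. No priority is stated for that case.

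A reader might also infer that the trial is biased or underpowered. It is neither on this ground. Randomisation keeps the change-score and level comparisons unbiased on average, and the 80% power stands.

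The size of the gain is uncertain. Rho appears nowhere in the documents, and at 0.9 the gain in power is only about two points. Equal variances are an assumption, and ART started during follow-up could make the variances differ. The efficiency argument is for linear models; under the median-regression fallback, adjusted and unadjusted analyses need not target the same quantity.

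The extra change-from-baseline row in SAP 5.1 is not a defect in itself, since it reads as a supporting analysis. The mixed models in SAP 5.4 use repeated measures but are additional analyses and do not alter the primary one.

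Last, baseline IFABP and LBP cannot be called already measured. They are late replacements, absent from the SAP 4.5 list. Protocol 3.6.B supports only stored plasma.

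**Conclusion.** The point holds as one of efficiency and prespecification. No primary or secondary model fixes the outcome's own baseline value as a covariate, and the conditional route is undefined. Power for the plan's 10-point VACS difference would rise from 80% to between about 82% (rho 0.9) and 94% (rho 0.3). This assumes equal variances, an SD of change of 25, 100 per arm and a linear model; with unequal variances the gain can shrink to nothing. For outcomes analysed as levels, variance falls by rho². The change is worth making, but the trial's validity does not depend on it.

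**What to change.** In SAP 5.2 and protocol 8.1:

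1. Make the baseline value of the same outcome, on the scale on which the outcome is analysed, a mandatory covariate in every primary and secondary model. The VACS outcome can stay a change score: in a linear model on the untransformed scale, adjusted change and adjusted 18-month value give the same treatment estimate.
2. Exempt that covariate from the r > 0.4 exclusion and from selection by observed imbalance.
3. In SAP 5.1, name the baseline-adjusted 18-month comparison as the main analysis for the Reynolds score and each biomarker, with change from baseline as supportive.
4. In SAP 5.3, state that the baseline outcome is in the imputation model. The current text makes multiple imputation the primary ITT analysis but lists no variables.
5. For IFABP and LBP, apply this where baseline values are assayed from the stored plasma.

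The cost is wording for VACS, CD4, Reynolds score, IL-6, D-dimer and sCD14, whose baseline values the SAP already plans to tabulate. For IFABP and LBP it may include baseline assays.
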